#### Electromyography

The DIS has no external validation. We decided that Surface Electromyography (EMG) might provide an impression of muscle activity level underlying dystonia. Therefore, surface EMG measurements will be carried out to determine mean EMG activity in individually determined muscle groups and in multiple conditions such as rest and during activities.

#### Spasticity

The soleus Hoffmann-reflex (H-reflex) represents excitability of the neural components of the stretch reflex arc
[22]. The H/M-ratio of the H-reflex represents an increased excitability of soleus motor neurons. The H/M-ratio is increased in subjects with spasticity due to various origins,
[23] and it has been shown that the H_max_ decreases significantly after ITB administration in children with spastic cerebral palsy when compared with baseline measurements. This represents a decrease in motor neuron excitability. Furthermore, the response appears to be dose-dependent
[22]. Although not all children tolerate the measurements, feasibility of the H-reflex was 93% in a study by Hoving and co-workers
[22].

For clinical assessment of spasticity in children with central motor disorders, the spasticity test (SPAT) is used during standard physical examination. When using the SPAT, we will follow a standardized protocol as described in the guideline for standard physical examination of children with central motor disorders
[24,25]. The difference between the range of motion and the angle of catch will be used as the outcome measure for spasticity
[26]. The test takes approximately 5 to 8 minutes per limb to perform
[25]. This test might be difficult to perform in children and adolescents with severe dystonia and its usefulness will become evident during the study.

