### Treatment

The results of pharmacological treatment of severe dystonic CP have been rather disappointing. Positive effects on dystonia with levodopa, anticholinergic drugs or muscle relaxants including benzodiazepines and baclofen, have been reported by some authors
[4,5]. In addition, Albright and co-workers described an anti-dystonic effect of intrathecal baclofen (ITB) treatment. Despite the fact that studies on the effects of ITB on dystonic cerebral palsy are limited in number and the level of evidence is low, ITB is now common practice in the treatment of severe dystonic CP.

Not all patients are eligible for ITB treatment. The following criteria apply: 1. The etiology is preferably known; 2. Management of aggravating factors, such as pain and discomfort, should be optimal; 3. Other treatment options should have been explored. Oral pharmacological treatment with levodopa, anticholinergic drugs or muscle relaxants including benzodiazepines and baclofen must have been attempted and must have resulted in high oral dosages with either unacceptable side effects or insufficient efficacy; 4. The movement disorder should be so severe that it interferes with activities of daily life or quality of life; 5. Treatment goals should be clear and applicable and, to avoid disappointment, it is important that patients and parents understand these goals; 6. Patients and parents should be motivated and able to adhere to the requirements of treatment, such as the frequent pump fillings and checkups in the outpatient clinic; 7. Patients should have sufficient body size to allow pump implantation
[6].

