### Objectives

The primary objective of the present study is to show whether ITB treatment improves activities of and participation in daily life (for example dressing, transfer, sitting in a wheelchair, hygienic care, speech) in dystonic CP patients. Certain patient characteristics, such as the location and severity of MRI lesions and Gross Motor Functioning Classification Score (GMFCS) level, might influence the effects of ITB treatment in patients with dystonic CP. Therefore, we will study whether individual patient characteristics (GMFCS, gender, age, MRI findings and co-medication) influence outcome and could be used in determining the indication for ITB in future patients. A secondary objective is to provide evidence for the effect of ITB on the level of body functions. The relevant clinical questions to be addressed are: 1. Does ITB decrease dystonia? 2. Does ITB decrease spasticity in dystonic patients? 3. Does ITB decrease pain? 4. Does ITB increase comfort? 5. Does ITB influence screening results of sleep-related breathing disorders? 6. What are the side effects of ITB?

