### Participants

Thirty subjects will be recruited from the outpatient clinics of the pediatric neurology and pediatric rehabilitation departments of the VUMC and the MUMC. Table 
1 shows the inclusion and exclusion criteria. We selected ages between 4 and 25 years old because older patients often show secondary complications, such as contractures, that could introduce greater variation into both the effects of treatment and treatment goals. Furthermore, to achieve a homogeneous patient group, only GMFCS IV and V (non-walkers) will be included. All patients and/or their caregivers will sign an informed consent form before participating in the study.

**Table 1 T1:** Summary of inclusion and exclusion criteria

**Inclusion criteria**	**Exclusion criteria**
• Dystonic cerebral palsy	• Contra-indications for general anesthesia
• GMFCS IV or V	• Contra-indications for baclofen
• Eligible for ITB treatment using criteria of common practice	• Oral pharmacological treatment is sufficient
• Lesions on MRI (cerebral white matter, basal ganglia, central cortex)	• Inadequate knowledge of Dutch language
• Aged 4 to 25 years old	• Deep brain stimulation
• Able and willing to complete study protocol	• Ventriculoperitoneal drain
• Consensus about inclusion	• Other disorders interfering with treatment

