#### Univariate analysis

The GAS t-scores, BAD score, SPAT score and EMG activity in the placebo and ITB group will be compared using an independent samples t-test. If the assumption of normality appears not to be valid, the non-parametric Mann–Whitney test will instead be used. A p-value of 0.05 is considered statistically significant for this primary analysis. To assess within-group changes in means between follow-up times and baseline GAS t-scores, BAD score, DIS score, SPAT score and EMG activity, a paired t-test or non-parametric Wilcoxon test will be used (depending on whether the normality assumption is valid). In these analyses, a p-value of 0.05 is considered to be statistically significant.

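### The between-group SPAT comparison may be selected on month-3 testability, which depends on dystonia that ITB is expected to reduce

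*Protocol article*

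**What the plan says.** The Objectives section of the protocol article asks, as its second question on body functions, "Does ITB decrease spasticity in dystonic patients". The Spasticity section defines the SPAT outcome: "The difference between the range of motion and the angle of catch will be used as the outcome measure for spasticity". Both angles must therefore be obtained. The same section closes its account of SPAT with the caveat "This test might be difficult to perform in children and adolescents with severe dystonia and its usefulness will become evident during the study".

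The Univariate analysis section attaches no condition to that outcome: "The GAS t-scores, BAD score, SPAT score and EMG activity in the placebo and ITB group will be compared using an independent samples t-test". Within-group changes from baseline are described separately, with paired tests.

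The article also expects treatment to act on the factor that makes the test difficult. The first question on body functions is "Does ITB decrease dystonia", and the Treatment section reports that earlier work "described an anti-dystonic effect of intrathecal baclofen (ITB) treatment". Severe motor impairment is the rule in this population: "only GMFCS IV and V (non-walkers) will be included".

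The Spasticity section also describes the H-reflex, but the Univariate analysis section does not list it. SPAT is the only spasticity measure named in the tests there.

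**The concern.** The article names a factor that can stand in the way of a SPAT measurement (severe dystonia), expects ITB to change it, and then compares the arms on SPAT. Suppose a child who cannot be tested at month 3 has no value. If ITB reduces dystonia, some severely affected ITB children can be tested while comparable placebo children cannot. The t-test then compares two groups that randomisation no longer makes alike. A generic complete-case rule would not cure this, because the chance of a value depends on treatment through dystonia.

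If more dystonic children are also more spastic, the placebo arm keeps its milder children and ITB looks worse on spasticity than it is. With 15 children per arm, a few untestable children are enough to unbalance the comparison.

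**Working it through.** **The plan's own figure.** The article gives no sample size, feasibility rate or effect size for SPAT. Its 13 per group is for GAS and reproduces: difference 12.5, pooled SD √((8.5² + 10²)/2) = 9.28, two-sided 5%, exact t power 0.883 at 12 and 0.909 at 13 per group. It has no bearing on this point.

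**Inputs.** From the documents: 15 children per arm and the t-test. Assumed, because the documents do not give them: the share of placebo children untestable at month 3 (20%, 30%, 40%), the ITB effect on dystonia (0.5, 1.0, 1.5 SD), the dystonia-spasticity correlation ρ (0.3-0.6), no true ITB effect on spasticity, comparison of month-3 levels, and no value for an untestable child.

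**Formula.** Let dystonia severity without treatment be standard normal and the test be possible below a cut-off c. ITB lowers severity by s, so an ITB child is testable if untreated severity is below c + s. With λ(a) = φ(a)/Φ(a), the apparent difference in SPAT, ITB minus placebo, in SD units is

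bias = ρ × [λ(c) − λ(c + s)].

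**Middle case: 30% untestable on placebo, s = 1.**
- c = Φ⁻¹(0.70) = 0.524
- λ(0.524) = 0.3477/0.70 = 0.497
- λ(1.524) = 0.1248/0.9363 = 0.133
- Untestable on ITB: 1 − 0.9363 = 6.4%, against 30% on placebo
- bias = 0.363ρ, that is 0.11 SD at ρ = 0.3, 0.18 at 0.5 and 0.22 at 0.6

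**Whole grid (multiplier of ρ).**

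| Placebo untestable | s = 0.5 | s = 1.0 | s = 1.5 |
|---|---|---|---|
| 20% | 0.172 | 0.274 | 0.324 |
| 30% | 0.218 | 0.363 | 0.444 |
| 40% | 0.256 | 0.441 | 0.555 |

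The extremes are 0.3 × 0.172 = 0.05 SD and 0.6 × 0.555 = 0.33 SD. With ρ = 0 or s = 0 the bias is zero. With ρ negative the sign changes.

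**Consequence for the test.** In a simulation of the middle case with ρ = 0.5 (15 per arm, 20,000 trials), on average 10.5 placebo and 14.0 ITB children have a value and the nominal 5% test rejects in 7.3% of null trials. The standard error is about √(1/10.5 + 1/14) = 0.41 SD, so a bias of 0.18 SD is a little under half a standard error. Over a wider set of assumptions (10-50% untestable, s = 0.5-1.0, ρ = 0.3-0.7) the bias is 0.03-0.36 SD and the type I error about 5-13%.

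**Effect of fixing the set at baseline.** In a simulation of the middle case with ρ = 0.5, limiting the comparison to children testable at baseline lowers the bias from about 0.17 to 0.05 SD and the type I error from 7.4% to 4.8%. Some bias remains when children testable at baseline become untestable by month 3. If placebo severity did not move at all, none would remain.

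**The case against.** **Difficult is not the same as missing.** A reader might infer that SPAT has a value only where dystonia allows it. The article says the test might be difficult. That could mean noisier readings, and since the test is done limb by limb, a child may lose some limbs and not all. This stands: the selection is conditional on untestable children having no value.

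**Missing-data rules belong in the analysis plan.** A general rule may well exist elsewhere, and its absence from an article is no finding. The point here is narrower: the article itself states a mechanism tied to treatment and fixes an unconditional between-group test beside it.

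**The comparison might be of change scores.** Children untestable at baseline would then have no change score in either arm, and most of the differential selection would disappear. The article treats the GAS effect as change, so this reading is possible. But the Univariate analysis section lists scores for the between-group test and describes changes separately, so the literal reading is follow-up levels. The objection supports the remedy below.

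**The direction is not given.** No dystonia-spasticity correlation is stated. The Classification section links milder MRI patterns to dyskinetic cerebral palsy and the severe pattern often to purely spastic paresis, so a zero or negative correlation cannot be excluded. This stands.

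**Outcome selection.** A reader might infer that SPAT can be kept or set aside once results are visible. The documents do not support that. The remark on usefulness is not a keep-or-drop rule, the Statistics section commits SPAT to tabulation and testing, and researchers and assessors are blinded. What remains is only that no time point is given for judging feasibility.

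**Worst-rank scoring looks like a natural check, but is unsound here.** Ranking children untestable because of dystonia as worst on spasticity counts a dystonia effect as a spasticity effect. In the middle case with no true spasticity effect, such a Mann-Whitney test rejects in about 12-19% of trials for ρ between 0.5 and 0, nearly always in favour of ITB.

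**Conclusion.** The point holds in a conditional form. If children who cannot be tested at month 3 have no SPAT value and levels are compared, the comparison may be selected on a variable that treatment affects. Under the assumed inputs the bias is about 0.05-0.33 SD against ITB. It vanishes without a correlation or without an effect on dystonia, and it reverses with a negative correlation. None of these inputs comes from the documents.

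A reader might go further and infer that a true reduction in spasticity will be masked or that a null effect will look like harm. A middle-case bias under half a standard error does not support either as an expectation. One secondary outcome is affected; the primary GAS analysis is not. The change is still worth making, because the remedy costs little and removes most of the bias in the case simulated.

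**What to change.** 1. Restrict the between-group SPAT comparison to children, and to limbs or muscles, in which the test could be performed at baseline. Preferably analyse change from baseline or adjust for the baseline value.
2. Report by arm and visit how many children and limbs could not be tested, and why.
3. Settle whether SPAT is retained from pooled, blinded baseline feasibility, before any month-3 value is seen by arm.
4. Do not add a worst-rank sensitivity analysis for untestable children.

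The cost is protocol and analysis wording, plus a recorded reason whenever the test cannot be done. The price is that children untestable at baseline do not contribute to this comparison, so its result applies to those in whom the test is possible before treatment.

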#### Pain and comfort

Parents will score pain and comfort on a visual analogue scale (VAS). The VAS is a straight 10 cm long horizontal block consisting of 10 smaller blocks with anchor points at 0 and 10. For pain, a score of 0 represents ‘no pain’ and a score of 10 represents ‘the worst possible pain’. For comfort, a score of 0 will represent being ‘very uncomfortable’ and a score of 10 is having ‘no problems at all’. If patients are able to indicate their mood, it will be scored by pointing out the applicable happy face, with choices of six faces ranging from very happy to very sad.

#### Sleep-related breathing disorders

Children with CP have a higher risk of sleep-related disorders than typically developing children
[27]. Bensmail et al. showed that patients with severe spasticity due to spinal cord injury and multiple sclerosis, treated with ITB by bolus administration, showed an increased respiratory disturbance index (the number of apneas/hypopneas per hour of sleep)
[28,29]. Polysomnography is the gold standard when measuring sleep-related breathing disorders (SRBD). However, this time-consuming and burdensome diagnostic test is not practical for children participating in research
[30]. A subscale of the Pediatric Sleep Questionnaire was developed to measure SRBD. This scale consists of 22 items and can be completed in five minutes. Sensitivity and specificity are high (81% and 87%). The scale is positive for a high risk of SRBD when there are 8 or more positive answers to the 22 question items (≥33%)
[30]. As the burden of a questionnaire is low for the patients and their families, as compared to polysomnography, we will use this questionnaire to determine if ITB changes the risk of SRBD.

#### Classification

For classification of the severity of motor abilities we will use the GMFCS
[31,32] and the Manual Ability Classification System (MACS)
[33,34]. GMFCS and MACS classification will be scored at baseline, 3 months and at twelve months. In a study by Voorman and co-workers, 74% of children with CP had restrictions in communication
[35]. Since many children with severe CP (GMFCS IV and V) cannot speak, assessment of language abilities cannot be based on speech production. In addition, language comprehension skills are difficult to assess in children with severe CP. Therefore, we will use the Computer-Based Instrument for Low motor Language Testing (C-BiLLT) to measure comprehension of spoken language at baseline. The validity of this instrument has been tested
[36]. We do not expect changes in outcomes on the C-BiLLT with ITB treatment since comprehension of spoken language is highly correlated with cognition, and cognition is not effected by ITB treatment. We will use the outcome of the C-BiLLT as a patient characteristic.

Magnetic resonance imaging (MRI) will be used to classify the severity of damage to the gray matter structures (cortex and basal ganglia) and white matter (loss of white matter and gliosis). The severity of brain damage on MRI can be classified in three groups; mild, moderate and severe. The mild pattern includes involvement of nucleus lentiformis and ventro-lateral thalamus, the moderate pattern includes additional involvement of the peri-central region and the severe pattern includes additional involvement of the entire thalamus and hippocampus. In the mild and moderate damage groups, infants suffer from the dyskinetic form of cerebral palsy, whereas the severe type of damage frequently produces purely spastic paresis
[3]. MRI studies of the brain are necessary to confirm the diagnosis of cerebral palsy. If MRI studies have been conducted previously, these studies will be critically assessed. If the quality is good, the MRI will be accepted and no further imaging is needed. If the quality of the MRI images is poor, the patient will undergo a new MRI including diffusion tensor imaging (DTI). If a patient had not yet undergone a MRI, one will be made including DTI. Adding DTI images to a regular MRI scan will require an extra scanning time of approximately four minutes. In this patient category MRI imaging has to be done under general anesthesia, since dystonic movements interfere with MRI quality.

#### Other study parameters

To assess the safety of ITB treatment, side effects and complications will be closely monitored. The complication rate will be calculated by dividing the number of complications by the duration in years of pump implantation.

Functional abilities at baseline will be assessed by the Paediatric Evaluation of Disability Inventory (PEDI) and will be repeated after three and twelve months. The PEDI was developed for children from six months to seven and a half years of age and assesses skills in mobility, self-care and social function. It can also be used for older children if their functional abilities are expected to be below the level of a child of seven and a half years old. The functional scales indicate if children with disability are able or unable to perform certain activities. Separate measures assess the degree of caregiving assistance and equipment modification that is needed to accomplish complex functional skills. Scores on the caregiver assistance scale are noted on a range from independent to maximal assistance and modification scores are scored as none, child-oriented, rehabilitation-oriented or extensive
[37,38]. The PEDI will be administered through direct assessment by a therapist.

### Randomization, blinding and treatment allocation

Subjects will be randomized in two groups by block randomization. Randomization will be done by the pharmacies of the VUMC and the MUMC. The pharmacist will be the only holder of the code for randomization. In case of emergency, the code will be accessible 24 hours per day and 7 days per week via either the pharmacist of the VUMC or MUMC or by opening a sealed envelope containing the subject’s group, available at the departments concerned. Allocation will be concealed, and the researchers, assessors and the physician responsible for pump filling will be blinded.

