## Methods/Design

### Study design

The design of the study is a double blind placebo-controlled multi-center randomized clinical trial. It will be conducted in the VU University Medical Center (VUMC) in Amsterdam and the Maastricht University Medical Center (MUMC) in Maastricht (both in the Netherlands). The Medical Ethical Committee of the VU University Medical Center approved the study. In both centers local practicability was granted subsequently. Subjects will be included over a period of two and a half years and they will participate in the study for one year. Figure 
1 shows the flow scheme for subjects and timing of measurements throughout the study.

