### Sample size calculation

We will use goal attainment scaling (GAS) as our primary outcome measure. The within group change for the placebo group is anticipated to be 0, with a standard deviation (SD) of 8.5. For the intrathecal baclofen group, the within group change is anticipated to be 12.5, with a SD of 10. To achieve a power of 90% when testing for a difference in means using a two-tailed independent samples t-test and a significance level of 5%, a total of 13 subjects per group will be needed.

In a previous study in the VU University Medical Center, 4 infections occurred in 34 pump implantations
[7]. Ward and coworkers reported pump removal in 5.9% of the cases with infections following implantation
[8]. Extrapolating these numbers, inclusion of 30 patients is expected to lead to 3.5 infections and 1.2 pump removals. To prevent the study from becoming underpowered, due to unexpected protocol violations or subject dropout due to complications other than those related to intrathecal baclofen treatment, we will include 15 subjects per group.

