#### Multivariate analysis

A multivariate analysis will be used to determine the effect of ITB treatment (primary: functional outcome; secondary: dystonia and the interaction with GMFCS, MACS, MRI classification and use of co-medication).

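### The primary t-test leaves out centre in a two-centre, block-randomised trial: some precision is lost if the centres differ, and the test is conservative only if blocks are formed within centre (minor)

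*Protocol article*

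**What the plan says.** All of this is in the protocol article.

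- **Centres** (Study design): "It will be conducted in the VU University Medical Center (VUMC) in Amsterdam and the Maastricht University Medical Center (MUMC) in Maastricht".
- **Allocation** (Randomization, blinding and treatment allocation): "Subjects will be randomized in two groups by block randomization", followed by "Randomization will be done by the pharmacies of the VUMC and the MUMC". The section names no block size and no stratification factor. It does not say whether each pharmacy has its own list or both work from one.
- **Primary comparison** (Univariate analysis): the GAS T-score, and likewise the BAD, SPAT and EMG measures, of the two arms "will be compared using an independent samples t-test". A Mann-Whitney test takes its place when normality fails. Neither version has a centre term.
- **Further modelling** (Multivariate analysis): for dystonia, the listed terms are "secondary: dystonia and the interaction with GMFCS, MACS, MRI classification and use of co-medication". Centre is not among the factors named.
- **Planning figures** (Sample size calculation): "The within group change for the placebo group is anticipated to be 0, with a standard deviation (SD) of 8.5" and "For the intrathecal baclofen group, the within group change is anticipated to be 12.5, with a SD of 10". The calculation is a two-sided t-test at 5% with 90% power, giving 13 per group, and 15 per group are to be enrolled.

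**The concern.** There are only two centres, and some features of the primary outcome depend on the local team. Goals are set with the team's help and goal levels are defined by the investigator (Primary outcome measure). A mean difference between centres in the GAS T-score is therefore possible.

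If it exists, a two-sample t-test puts it into the residual variance, which widens the confidence interval. If allocation is also balanced within centre, the treatment difference is free of the centre effect but its estimated standard error is not. The test then rejects less often than its nominal 5%.

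Baseline adjustment cannot recover this precision. Every goal starts at -2, so the baseline T-score is the same constant for every patient. Centre is one of the few design factors that could help. At stake is modest precision in a 30-patient trial, not the validity of its conclusion.

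**Working it through.** **Inputs from the article.** Treatment difference 12.5; SD 8.5 (placebo) and 10 (ITB); two-sided 5%; 13 evaluable and 15 enrolled per group; two centres.

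**Assumptions not in the article.** Blocks of 4; centre split 15/15 or 20/10; centre difference d of 0, 2.5, 5 or 10 T-points added to the planning SDs; blocks either within centre or from one common list.

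**1. The article's sample size.** Pooled SD = √((8.5² + 10²)/2) = √86.125 = 9.28. Exact t-test power is 88.3% at 12 per group, 90.9% at 13 and 94.5% at 15. The stated 13 per group reproduces.

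**2. Scale of a centre difference.** With three goals, weight 1 and ρ = 0.3, one level on one goal is 10/√(0.7×3 + 0.3×9) = 10/√4.8 = 4.6 T-points. The baseline is 50 − 60/√4.8 = 22.6 for every patient. So 5 points is about one level on one of the three goals, and 5/9.28 = 0.54 SD. Ten points is about two levels in total, and 10/9.28 = 1.08 SD.

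**3. What the formula predicts.** With equal centres, ignoring centre adds about d²/4 to the variance.

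- d = 5: SD = √(86.125 + 6.25) = 9.61.
- d = 10: SD = √(86.125 + 25) = 10.54.

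With blocks within centre, the true standard error is smaller than the estimated one by 9.28/9.61 = 0.966 or 9.28/10.54 = 0.880. The critical value on 28 degrees of freedom, 2.048, then acts like 2.048/0.966 = 2.12 or 2.048/0.880 = 2.33. The actual alpha is about 0.043 or 0.027.

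**4. Simulation at 30 patients** (20,000 null and 10,000 alternative runs per setting).

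| Scheme | Split | d | Alpha, unadjusted | Power, unadjusted | Power, with centre |
|---|---|---|---|---|---|
| Blocks within centre | 15/15 | 0 | 0.050 | 94.3% | 94.0% |
| | | 2.5 | 0.050 | 94.3% | 94.5% |
| | | 5 | 0.042 | 93.7% | 94.5% |
| | | 10 | 0.028 | 89.4% | 94.0% |
| Blocks within centre | 20/10 | 5 | 0.042 | 93.9% | 94.5% |
| | | 10 | 0.027 | 90.6% | 94.2% |
| One common list | 15/15 | 0 | 0.049 | 94.6% | 93.7% |
| | | 5 | 0.050 | 93.3% | 94.0% |
| | | 10 | 0.048 | 88.0% | 93.6% |
| One common list | 20/10 | 5 | 0.052 | 93.3% | 93.9% |
| | | 10 | 0.051 | 88.7% | 94.0% |

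The alpha column agrees with step 3. The centre-adjusted model keeps alpha at 0.047 to 0.053 in every setting. At d = 10 the power loss is 3.5 to 4.6 points with blocks within centre and 5.3 to 5.7 points with a common list.

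**5. Simulation at 26 patients, blocks within centre, 13/13 split.** Unadjusted against adjusted power is 90.8% against 90.6% at d = 0, 89.2% against 90.3% at d = 5, and 84.8% against 90.8% at d = 10. This size is relevant because patients who withdraw after implantation are neither replaced nor analysed (Withdrawal of individual subjects).

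**6. If the planning SD already contains the centre variance.** Holding total SD at 9.28 with 13 per group and about equal centres, a centre share of 10% means a difference of 2×√0.10×9.28 = 5.9 points. Alpha is then 4.0%, and power is 91.6% unadjusted against 93.2% adjusted. A share of 20% means 2×√0.20×9.28 = 8.3 points, with alpha 2.9% and power 92.9% against 95.8%.

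**The case against.** **Blocks within centre are inferred, not stated.** This stands. A reader might infer from the two pharmacies that allocation was stratified by centre and that the true type I error is therefore below 5%. The article does not support that inference. The same section refers to a single pharmacist holding the code and makes the code available through either pharmacy, which would also fit one shared list. Under a common list the simulated alpha of the unadjusted test stays at 0.048 to 0.052. Such details are also commonly left to the full protocol, so their absence is no fault.

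**The harm is small.** This stands for moderate centre differences. A loss of 4 to 5 points needs a centre difference above one SD, or 10/12.5 = 80% of the assumed treatment effect, and nothing in the article points to one that large. If the planning SD already contains centre variance, unadjusted power stays above 90% even at 13 per group.

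**The outcome is standardised.** Recording is identical across measurements and a blinded assessor rates the videos, which limits rating differences. It does not remove differences in how demanding the goals are. Local dose adjustment is a weaker source: it cannot act pharmacologically in the placebo group, so it would produce a treatment-by-centre interaction, which an additive centre term does not model.

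**The t-test is valid and matches the sample size calculation.** This is right. The point concerns efficiency. It remains a point about stated text, because the article names the primary test and that test has no centre term.

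**Conclusion.** The point holds as a minor, conditional one. Ignoring centre does not make the primary test anti-conservative under either randomisation scheme, and the stated sample size is unaffected. If the centres differ, some precision is lost under both schemes. At 30 patients the loss is about 1 point of power or less up to 5 T-points and about 4 to 5 points at 10 T-points (3.5 to 5.7 across the scenarios run).

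Conservatism is an additional consequence only if blocks are formed within centre. Actual alpha is then about 0.04 at 5 points and 0.03 at 10. All these sizes rest on assumed centre differences, block size and centre split.

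**What to change.** - Analyse the three-month GAS T-score with a linear model containing treatment and centre as fixed effects, and report the adjusted mean difference with its 95% CI.
- Use the same centre term where BAD, SPAT and EMG activity are compared between groups.
- Replace the Mann-Whitney fallback by its centre-stratified version, the van Elteren test.
- Say whether blocks are formed within centre. Prespecify the centre term in either case.

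The cost is a few words of analysis text and one degree of freedom, with no new data or procedures. If the centres do not differ, the simulated power cost at 30 patients is 0.2 to 0.3 points with blocks within centre. With a common list it is under 1 point (94.6% against 93.7% at a 15/15 split), because chance imbalance between centre and arm adds a little variance.
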